### Randomization, blinding and treatment allocation

The study is participant- and outcome assessor-blinded. Allocation to intervention order will be randomized by a computer-generated randomization scheme in *R* using block randomization. The lab technician is not blinded for safety and monitoring purposes and will oversee the randomization process. Although ventilation is expected to increase with ~ 20% mostly due to increased tidal volume and possibly respiratory rate, the extensive evidence-based experience of the study team and study advisors is that participants will not notice changes in their breathing at an F_I_O_2_ of 0.16 [50–53]. Indeed, blinding was assessed and successful in our latest hypoxia trial in PD where participants were exposed to multiple independent interventions of continuous and intermittent mild to moderate hypoxia (manuscript submitted).

### Study procedures

#### Screening procedure

First, participants will fill in an online questionnaire (Appendix I) about cardiac or pulmonary diagnoses or symptoms and smoking, to exclude individuals with relevant cardiorespiratory abnormalities. If this questionnaire does not yield any exclusion criteria, participants are invited for an in-hospital screening procedure.

During this screening procedure, informed consent will first be ascertained, and the informed consent form will be signed. Subsequently, participants will be screened for cardiac abnormalities using an electrocardiogram and blood for baseline measurement is drawn and processed per standard plasma procedures. Then, participants undergo neurological testing, and finally participants will be blindly exposed to the active study intervention under arterial blood gas (ABG) and cardiopulmonary monitoring of an experienced pulmonary lab technician. ABG will be taken at the start of the intervention, and in the last 5 min of hypoxia. If oxygen saturation reaches 82%, an extra ABG will be taken in-between to investigate arterial pO_2_. Stop criteria during this intervention are pre-defined (Appendix II). Continuous non-invasive cardiorespiratory monitoring is conducted using the Cosmed® metabolic monitoring system (*Quark* metabolic cart for cardiopulmonary exercise testing [CPET], *COSMED Srl*, The Metabolic Company, Italy).

#### Intervention procedures

Interventions will be conducted three times a week, for four weeks in total. The first intervention will take place in the hospital under supervision of a pulmonary technician. Any subsequent intervention will take place at home, with a pulmonary technician present for instructions and monitoring at least once. If necessary for safety purposes, this technician will be additionally present for one or more subsequent interventions. After that, remote expert assistance is present through a live (video)call during each session in the first intervention week. Supervision can be extended when necessary for safety during subsequent weeks. Mandatory weekly videocalls ascertain adequacy of administration, safety and compliance. Participants are explicitly encouraged to spread the three interventions over any week as much as possible. By exception, an occasional intervention on the day following a previous intervention will be allowed.

Before the first session, the pulmonary technician will explain the working mechanism of the machine and will give ample time for questions. This includes the auto-off function of the machine, and when to contact the study team. When one individual has completed the Intervention phase, the machine will be collected and will be delivered to the next participant. In-between, machine parts that are part of the breathing circuitry will be cleaned for re-use.

### Outcome measurement

Participants will be tested in-clinic for all secondary outcome measures except PDQ-39 in a practically defined OFF-medication state (> 12 h after intake after the last dose of dopaminergic medication). This OFF testing will be conducted in the morning and is a widely used and proportional method of ascertaining no relevant effects of exogenic dopamine on outcome measurement [54–58]. PDQ-39 is filled in by participants through an online survey. Because driving capability may be influenced by being OFF, we ask participants to refrain from driving to the in-hospital appointments themselves. Instead, they may be driven by partner, family, acquaintance or public transport. Travel expenses for clinic visits are covered.

### Statistical analysis

#### Primary study outcomes

Safety (i.e., number and nature of adverse events) and the feasibility (i.e., questionnaire (details)) will be analyzed using descriptive statistics.

#### Secondary study outcomes

Secondary study outcomes (functional and motor testing, and plasma markers of target engagement) will be analyzed by linear mixed models (for linear effects between T0, T1 and T2), and if applicable, with post-hoc analyses using ANOVA.

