### Secondary objectives

(ii)to explore the net effects of a 4-week intermittent hypoxia protocol on a battery of standardized and functional scales, including Movement Disorders Society-Unified Parkinson’s Disease Rating Scale parts II and III.(iii)to assess the net effects of a 4-week intermittent hypoxia protocol on plasma biomarkers, indicative of neuroprotective pathway induction.

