### Measurement frequency

In-clinic measurements will be performed at baseline, in the week after the 4-week intervention period and 4 weeks after the last intervention session, except for the feasibility questionnaire that will be sent once, immediately after the intervention period. Adverse events are evaluated on a weekly basis.

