Some limitations of this study need to be considered. First, the intervention duration will likely be insufficient for structural or long-term symptomatic effects beyond the study period. Most previous studies that have investigated intermittent hypoxia in other populations have either not included long-term follow-ups or have not been able to show lingering effects beyond the intervention period [62, 78]. In this study, we therefore also included a longer-term follow-up of one month after the intervention period to assess the longer-term stability of effects on clinical symptoms and blood-based markers. Recent evidence suggests that interspersion of hypoxia with either hyperoxia or hypercapnia might respectively enable a more rapid recovery after hypoxia or enhance the potency of effect on mitochondrial metabolism, providing an opportunity for comparison to the current protocol [20, 79, 80]. This study includes a relatively low number of participants, which hampers its power to detect smaller treatment effects on several included standardized scales. Furthermore, this study design is unable to provide meaningful insight into the potential neuroprotective merits of intermittent hypoxia in PD, apart from yielding hypothesis-generating insights that may be derived from the plasma biomarker selection. Indeed, previous neurological biomarker studies in hypoxic training studies are limited to BDNF [81–85], demonstrating conflicting results. This highlights that despite the broad biomarker selection, biomarkers may only provide limited insight into the potential neuroprotective benefit.

In conclusion, intermittent hypoxia may represent a relatively simple, low-cost, and easily applicable and potentially scalable strategy that could be added to the current arsenal of non-pharmacological therapies for PD. This study is designed to investigate the safety and symptomatic effects of a multiple-week intermittent hypoxia protocol in PD and will thus provide essential insights for future studies to better understand its therapeutic potential in PD.

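### The secondary-outcome model is worded as a linear trend over T0, T1 and T2, which gives the end-of-treatment visit almost no weight and cannot separate effect from persistence

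*Protocol article*

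**What the plan says.** Under Statistical analysis, Secondary study outcomes, the protocol article plans "linear mixed models (for linear effects between T0, T1 and T2"), followed by the clause "and if applicable, with post-hoc analyses using ANOVA". This covers the functional and motor tests and the plasma markers.

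The visit schedule is in Measurement frequency: "In-clinic measurements will be performed at baseline, in the week after the 4-week intervention period and 4 weeks after the last intervention session". Intervention procedures gives the treatment period: "Interventions will be conducted three times a week, for four weeks in total". So T0 precedes treatment, T1 follows its end within about a week, and nothing is given between T1 and T2.

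The clinical secondary objective is to "explore the net effects of a 4-week intermittent hypoxia protocol on a battery of standardized and functional scales". The limitations paragraph of the Discussion says that "the intervention duration will likely be insufficient for structural or long-term symptomatic effects beyond the study period". It adds that most earlier studies in other populations either had no long-term follow-up or "have not been able to show lingering effects beyond the intervention period". It describes T2 as a "longer-term follow-up of one month after the intervention period to assess the longer-term stability of effects on clinical symptoms and blood-based markers".

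**The concern.** The article does more than leave the model open: it states a shape for time, and that shape does not match the design. A straight line through T0, T1 and T2 describes an effect that goes on growing at the same rate for about four weeks after treatment has stopped. Nothing in the protocol describes such a course.

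The design asks two questions: what the effect is at the end of the 4-week protocol (T1), and whether it is still there a month later (T2). One slope answers neither. A near-zero slope could mean no effect, or an effect at T1 that has gone by T2. A clear slope could come from T2 alone.

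At stake is how objectives (ii) and (iii) are read. A transient benefit on symptoms, or a transient rise in an injury marker such as GFAP or UCH-L1, could pass as no change and misinform the next trial.

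**Working it through.** The protocol gives no effect size, SD, correlation or power for the secondary outcomes, so there is no planned figure to reproduce. The check is in two parts: the weights, which depend only on visit times, and power, which needs assumptions.

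**Inputs from the protocol.** T0 at week 0; T1 in the week after a 4-week intervention, so week 4 to 5; T2 at about week 8; 20 per arm (Sample size calculation).

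**Assumed.** Arm difference of 0.8 SD at T1, a fraction f of it left at T2, equal correlation ρ = 0.5 to 0.8 between visits, two-sided 5% test, no dropout.

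**Step 1: weight of each visit.** With complete data and equal correlation, the slope weight of visit j is w_j = (t_j − t̄) / Σ(t_j − t̄)². Multiplying by the 8-week span puts it on the scale of the T0–T2 change. For weeks 0, 4.5 and 8: t̄ = 4.167, deviations −4.167, 0.333 and 3.833, sum of squares 32.17. The T1 weight is 8 × 0.333 / 32.17 = 0.083.

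| T1 at week | T0 | T1 | T2 |
|---|---|---|---|
| 4 | −1.00 | 0.00 | 1.00 |
| 4.5 | −1.04 | 0.08 | 0.95 |
| 5 | −1.06 | 0.16 | 0.90 |

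An effect present only at T1 therefore appears at 0%, 8% or 16% of its size. If half remains at T2, 50% to 61% appears. If baseline is taken 1 to 4 weeks before the first session (T1 at week 4.5), the T1-only share rises to 15–26%, which is still small.

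**Step 2: power of the arm-by-linear-time test.** Expected contrast = 0.8 × (w₁ + f·w₂), with w₁ and w₂ the scaled weights of T1 and T2. Its SE = 8 × √[2(1 − ρ) / (20 × Σ(t_j − t̄)²)]. With T1 at week 4.5 and ρ = 0.5, SE = 8 × √[1 / (20 × 32.17)] = 0.315; with ρ = 0.8 it is 0.200. Power is from the noncentral t with 38 df.

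| Effect left at T2 | Contrast, T1 at week 4.5 | Slope power, ρ = 0.5 to 0.8 |
|---|---|---|
| none (f = 0) | 0.07 SD | 5.5–6.2% |
| half (f = 0.5) | 0.45 SD | 28–59% |
| all (f = 1) | 0.83 SD | 73–98% |

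For f = 0, moving T1 across weeks 4 to 5 gives a range of 5% to 10%.

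**Step 3: comparators at T1, which do not depend on f.**
- T0-to-T1 change, unadjusted: SE = √[(2/20) × 2(1 − ρ)] = 0.316 to 0.200; power 69–97%.
- T1 adjusted for baseline: SE = √[(2/20) × (1 − ρ²)] = 0.274 to 0.190; power 81–98% (37 df).

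The change contrast is the like-for-like comparison with the unadjusted slope. The step from 69% to 81% at ρ = 0.5 comes from baseline adjustment, not from the handling of time.

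**Step 4: simulation.** Random-intercept mixed models were fitted to 300 simulated trials (ρ = 0.8, weeks 0, 4.5 and 8, full fading). The linear-time interaction was significant in 4% of runs, with a mean fitted 8-week difference of 0.09 SD. With categorical visit, the T1 term was significant in 99%, with a mean of 0.82 SD.

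**The case against.** **The wording may be loose.** The phrase could be shorthand for differences between named visits within a linear model, and post-hoc ANOVA fits naturally with visits as levels of a factor. That is possible. But the plain meaning is a linear trend, and the ANOVA clause is conditional and names neither visit nor contrast. If a significant trend is what triggers it, it would seldom be reached in the case that matters. Under either reading the sentence needs correcting.

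**The protocol does not predict fading by T2.** This stands. A reader might infer that the authors expect the effect to be gone at T2, but the documents do not say so. Their own statement concerns effects beyond the study period, and T2 lies inside that period. The remark on earlier studies combines those without long-term follow-up and those that found nothing lasting, and absence of follow-up is not evidence of fading. T2 is there to assess stability. Fading is a plausible course, no more.

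**With full persistence the slope performs well.** This also stands: 73–98%, against 69–97% for the change contrast. The loss depends on the course after T1, which the trial is meant to find out.

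**Model terms belong in the SAP.** A reader might infer from the sentence that no comparison between arms is planned. That is not supported. The objectives speak of net effects in a two-armed randomized trial, and an article may leave interaction terms and covariates to a fuller document. Their absence is no part of this point.

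**The outcomes are exploratory.** This is correct, and it limits the severity.

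**Conclusion.** The point holds in a limited form. As written, the model imposes a linear time course that does not match when treatment is given. It recovers 0–16% of an effect present only at T1, a result that needs only the visit times (with baseline at week 0). It also cannot separate the end-of-treatment effect from its stability at T2. The power figures rest on the assumed 0.8 SD effect, correlations of 0.5–0.8 and no dropout. Normal-approximation values differ from the noncentral-t values by about two percentage points or less.

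It would go too far to say that the analysis will report a real effect as nil. That follows only if the effect fades fully or nearly so and the trend is the sole result reported. Severity is moderate: the co-primary outcomes are analysed descriptively and are unaffected, and no confirmatory claim or decision rule depends on this model.

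**What to change.** In Secondary study outcomes, replace the bracketed phrase about linear effects with wording such as: *a linear mixed model with visit as a categorical factor, arm and arm-by-visit terms, adjusted for the baseline value; the arm difference at T1 estimates the effect of the 4-week protocol and the arm difference at T2, reported separately, estimates its persistence, each with a 95% confidence interval.* Either tie the post-hoc ANOVA to a stated contrast or drop it.

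The cost is one sentence, one extra degree of freedom for time, and a small loss of efficiency if the effect really is linear over the eight weeks. No new data or visits are needed.

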### Interim analysis

An interim analysis of study progress and safety will be performed after 20 individuals have completed the study. This will not involve a futility analysis because of the early phase of this clinical trial.

### Monitoring and registration

#### Quality assurance and monitoring

The study will be monitored regarding the health, safety and rights of participants, protocol adherence and quality of data and data reporting during this trial at study initiation, twice during the study (on-site) and once at study completion. On-site monitoring visits (performed by a specialized study monitor) will assess the progress of the study, study procedures, used study materials and identify any concerns that result from review of the subject Informed Consent documentation, study records, collected data and study management documents. The study monitor will also ensure the Investigator adheres to all applicable regulations.

### Data safety monitoring board

A data safety monitoring board (DSMB) will be established, which will consist of a PD-specialized neurologist, an anesthesiologist, a pulmonologist, an epidemiologist, and a patient representative. The DSMB will monitor the occurrence of adverse events and the study-related overall health of participants in this trial. An interim analysis will be performed after the successful completion of the study procedures by the first twenty participants to provide the DSMB with the latest recruitment data and safety outcomes, after which the Board will come to a consensus regarding study continuation or any adjustments. No member of the board has a conflict of interest with the sponsor of the study.

## Discussion

In this phase 1b-2a randomized controlled trial, we will for the first time assess the safety and net effects of a four-week intermittent hypoxia protocol in people with mild to moderate PD.

Various previous studies have investigated hypoxia in PD. These trials included both healthy adults (with or without intense exercise interventions in hypoxic conditions [35, 59, 60]) as well as individuals with cardiovascular or pulmonary disease [20–22, 61, 62]. As hypoxia protocols differ importantly between studies, we have weighed the evidence and created a balance between safety and efficacy [19]. In this, we specifically consider the respiratory dysfunction in people of older age, and even more in people with PD, including a reduced hypoxic ventilatory response [63–65]. Therefore, we deploy a slightly higher F_I_O_2_ than deployed in some other hypoxic training studies, although the proposed protocol is still regarded a potent stimulus [19]. 

Previous studies found increases in hematopoiesis and cardiovascular fitness for comparable protocols, assuring target engagement [31, 66, 67]. These previously established beneficial effects on cardiovascular function in healthy humans are the prime reason to include the 6MWT as a marker of light- to moderate-intensity endurance [68]. Further exploration into the mechanisms of action is a specific objective of this study, and therefore, a selection of putative plasma markers of neuroprotection and neuronal injury is included in this study. It should be noted that for various of these markers, sensitivity to hypoxia and post-exposure timeline are unknown.

The HIF-1 pathway, which is regarded the prime mediating pathway for adaptive responses to hypoxic training protocols, is increasingly regarded as a potential target for the development of small-molecule approaches that can activate neuroprotective pathways in PD [69]. Various studies have been conducted with HIF enhancers or inhibitors of prolyl hydroxylase, the enzyme that constitutively breaks down HIF in normoxic environments. These studies have demonstrated neuroprotection in basal ganglia in parkinsonian models [3, 15, 70, 71], primarily through improving mitochondrial biogenesis, turnover and electron transport chain efficiency, and subsequently decreasing oxidative stress and pro-apoptotic pathway induction [72–74]. This clinical study may therefore additionally accelerate the translation of such preclinical insights into a target for repurposed pharmacological compounds [69]. It should be noted that the hypoxia response pathway is largely, but not completely, HIF-dependent [75], and that HIF-1 activation in normoxic conditions is not disease-modifying in some preclinical models of neurodegeneration [6, 7]. 

A prime novelty of this study is the remote, home-based nature of administration of a hypoxic training protocol. To the best of our knowledge, this approach has not been performed previously in individuals with a neurodegenerative condition, although remotely administered hypoxic protocols have been proposed previously [76]. Important considerations for the home-based use of an hypoxic intervention include the feasibility of intermittent hypoxia as a non-pharmacological intervention. Although in-center protocols have also pursued multiple-week protocols, home-based administration is a necessity for feasible application of low-burden intermittent hypoxia protocols in long-term practice. The same argument holds for the scalability of the intervention, as well as the long-term compliance to interventions in PD [77]. 

Some limitations of this study need to be considered. First, the intervention duration will likely be insufficient for structural or long-term symptomatic effects beyond the study period. Most previous studies that have investigated intermittent hypoxia in other populations have either not included long-term follow-ups or have not been able to show lingering effects beyond the intervention period [62, 78]. In this study, we therefore also included a longer-term follow-up of one month after the intervention period to assess the longer-term stability of effects on clinical symptoms and blood-based markers. Recent evidence suggests that interspersion of hypoxia with either hyperoxia or hypercapnia might respectively enable a more rapid recovery after hypoxia or enhance the potency of effect on mitochondrial metabolism, providing an opportunity for comparison to the current protocol [20, 79, 80]. This study includes a relatively low number of participants, which hampers its power to detect smaller treatment effects on several included standardized scales. Furthermore, this study design is unable to provide meaningful insight into the potential neuroprotective merits of intermittent hypoxia in PD, apart from yielding hypothesis-generating insights that may be derived from the plasma biomarker selection. Indeed, previous neurological biomarker studies in hypoxic training studies are limited to BDNF [81–85], demonstrating conflicting results. This highlights that despite the broad biomarker selection, biomarkers may only provide limited insight into the potential neuroprotective benefit.

In conclusion, intermittent hypoxia may represent a relatively simple, low-cost, and easily applicable and potentially scalable strategy that could be added to the current arsenal of non-pharmacological therapies for PD. This study is designed to investigate the safety and symptomatic effects of a multiple-week intermittent hypoxia protocol in PD and will thus provide essential insights for future studies to better understand its therapeutic potential in PD.

## Appendix I

Have you experienced chest pain in the past 5 years?Have you fainted for an unexplained reason in the past 5 years?Are you short of breath or exhausted after short or mild exertion, such as climbing the stairs or running errands?Do you have heart failure or other heart disease?Do you become stuffy or short of breath when lying down (in bed)?Do you have (have you had) a heart murmur?Do any of your parents, brothers, sisters or your children under the age of 50 have heart disease (myocardial infarction, arrhythmia, hypertrophy, cardiomyopathy, pulmonary QT syndrome or dysrhythmia)?Did any of your parents, brothers, sisters or children die suddently/unexpectedly (sudden cardiac death)?Do you have high blood pressure requiring multiple medications?Do you smoke or have you smoked? No / Yes, namely: .Have you lived or worked in an environment where there was a lot of smoking or you breathed other polluted air? No / Yes, namely: .Do seasons, weather or air quality change your breathing to the extent that you may become short of breath or exhausted as a result?Do you have any lung disease (e.g. asthma, bronchitis/COPD, pulmonary fibrosis, interstitial lung disease, emphysema)? If yes (which disease, severity, medication).Do you often suffer from coughing or have a lot of trouble coughing up mucus?Do you have sleep apnoea (breathing stops during sleep)?On average, do you consume more alcoholic drinks than 3 units (men) or 2 units (women) per day?Does not taking your parkinsonian medication make you feel stuffy, short of breath or exhausted, or does not taking it cause you to wheeze or whoop?Do your parkinsonian symptoms become unbearable by delaying or not taking your morning medication?Has anything changed about your parkinsonian medication (different drug or dose) in the past month?Do you think you will need more or different parkinsonian medication in the next month?Do you have any treatments that you find difficult(er) to momentarily interrupt or should not interrupt (e.g. as per your neurologist’s strict instructions), such as medication patches, deep brain stimulation (DBS) or a medication pump?

